## Abstract

Child maltreatment is associated with life-long social, physical, and mental health problems. Intervening early to provide maltreated children with safe, nurturing care can improve outcomes. The need for prompt decisions about permanent placement (i.e., regarding adoption or return home) is internationally recognised. However, a recent Glasgow audit showed that many maltreated children “revolve” between birth families and foster carers. This paper describes the protocol of the first exploratory randomised controlled trial of a mental health intervention aimed at improving placement permanency decisions for maltreated children. This trial compares an infant's mental health intervention with the new enhanced service as usual for maltreated children entering care in Glasgow. As both are new services, the trial is being conducted from a position of equipoise. The outcome assessment covers various fields of a child's neurodevelopment to identify problems in any ESSENCE domain. The feasibility, reliability, and developmental appropriateness of all outcome measures are examined. Additionally, the potential for linkage with routinely collected data on health and social care and, in the future, education is explored. The results will inform a definitive randomised controlled trial that could potentially lead to long lasting benefits for the Scottish population and which may be applicable to other areas of the world. This trial is registered with ClinicalTrials.gov (NC01485510).

## 1. Background

Child maltreatment is known to be associated with significant problems in later life affecting both physical [1] and mental health [2–4]. Intervening early can improve outcomes when children's social and emotional development is at risk [5], and recovery from the effects of maltreatment is possible if children are provided with safe and nurturing care early, ideally in the first year of life [6–8]. Failure to do so puts children at risk of disrupted attachments and poor emotional well-being [9]. There is a growing international research and policy consensus on the need for prompt decisions about permanent placement (i.e., regarding adoption or return home) so that children can experience secure care as early as possible [9–14]. However, a recent audit of services in Glasgow revealed that children frequently “revolve” between maltreating birth parents and various temporary foster placements [10]. Moreover, there are no infant mental health services focusing on maltreated infants in Scotland.

There have been attempts to develop interventions to improve the mental health of maltreated infants [6, 7], but only one evaluated programme was identified, the Tulane Infant Team in New Orleans, Louisiana [8]. This is still in operation and aims to improve the permanency decision-making process using a comprehensive mental health intervention. Permanency decisions involve placing a child in the care of one family until the child reaches the age of independence. The Tulane Infant Team offers a tailored intervention to every family with a child coming into care. It assesses the quality of child's relationships and the degree of change over the course of the intervention. It makes considered recommendations to inform the legal system about the best placement outcome for each child. The aim of the Tulane Infant Team is to rehabilitate children back to their birth parents, and when this cannot be achieved safely or quickly enough, to free the children for adoption. An evaluation based on analysis of routine data was conducted four years prior to and four years after the introduction of this intervention to New Orleans [8]. This suggested that more children were adopted following its introduction; however, for those returned to birth families, there was a significant reduction in repeated maltreatment both for that child and subsequent siblings. The limitation of the study was a consecutive cohort design, and the lack of randomisation means that factors other than the intervention may be contributing to the positive effects. 

Deciding which are the most appropriate outcome measures for this population is challenging. Gillberg [11] described the high levels of coexistence between symptoms of different disorders in early childhood, which he defined as ESSENCE (Early Symptomatic Syndromes Eliciting Neurodevelopmental Clinical Examinations). This demonstrates the need for a diverse and thorough assessment across the various fields described by Gillberg [11], including general development, language, social interrelatedness, mood, and behaviour. 

The overall aim of this exploratory randomised controlled trial (RCT) is to evaluate the feasibility and to inform the design of a definitive RCT evaluating a Scottish adaptation of the New Orleans intervention for maltreated children. The specific research questions are as follows:what are the size and nature of any effects of the Glasgow version of the New Orleans model, the Glasgow Infant and Family Team (GIFT), on the mental health of maltreated preschool children?is a definitive multicentre RCT of GIFT feasible, acceptable, and necessary?what would be the required size of a definitive RCT of GIFT?what would be the optimal outcome measures for a definitive RCT of GIFT?what are the beliefs, attitudes, and experiences of those managing and delivering GIFT and an enhanced usual service, the Family Assessment and Contact Service (FACS)?is GIFT likely to be cost-effective in Glasgow and, if so, what design parameters are required for a definitive RCT?

## 2. Methods/Design

### 2.1. Study Design and Setting

This study is an RCT comparing two arms: GIFT (the intervention arm) and FACS (enhanced version of services as usual arm). Outcome measures from all participants are being collected one month after a child comes into care and then again one year later.

The study is set in the city of Glasgow, Scotland's largest and most ethnically diverse city with an estimated population of 588,470 of which almost 6% represent an ethnic minority (http://www.glasgow.gov.uk/index.aspx?articleid=3969). Children represent 16% of the Glasgow population; over one-third live in areas in the most deprived decile within Scotland, whilst only 3% live in areas in the least deprived decile within Scotland.

### 2.2. Participants

All parents (or recognised parental guardians) with a child aged between 6 and 60 months who come into a period of care due to child protection concerns are invited to take part in the study. Children are excluded from the study ifthey have a profound learning disability (as assessment outcome measures would not be appropriate), and/or their primary caregiver is unavailable to take part in the intervention (such as long-term imprisonment, death, or being uncontactable by services or research team for 3 months or more). 

### 2.3. Recruitment and Randomisation

Recruitment is taking place over 17 months from December 2011 to April 2013. An estimated 153 eligible children are expected to enter care due to maltreatment during this period, that is, 9 children per month. Consent from parents and foster carers to be approached by the research team to discuss the study is obtained by the social worker who gives the potential participants an information leaflet and a digital video disc explaining the study, its intent, and what participation would entail. Thereafter, informed consent from those agreeing to be contacted is obtained by the study's recruitment officer. 

An anticipated consent rate of 65% will include approximately 100 families in the study, with 50 children in each trial arm (Figure 1). The families are randomly allocated to GIFT or FACS by the Robertson Centre for Biostatistics. Children from the same birth family, regardless of placement, are assigned the same study arm to reduce contamination (as birth parents are the primary target of the intervention). Randomisation is also stratified by child's age (<2 and ≥2 years). The trial arm allocation is concealed from the researchers who carry out the baseline and follow-up assessments, and the first research assessment is carried out prior to randomisation.

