### 2.9. Data and Statistical Analysis

The study will be analysed using the intention-to-treat analysis. To make preliminary assessment of the efficacy of GIFT, changes in scores on the ITSEA competence scale will be compared between the GIFT and FACS groups, adjusting for important baseline variables. To assess feasibility, the percentage consenting and the retention rate will be estimated: whether these are related to social circumstances or the type of intervention will be investigated using routine data where possible. 

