### 3.1. Limitations

The GIFT team only has the capacity for a caseload of 50–60 children in one year. This limited capacity means that children removed from parents due to maltreatment but then placed in kinship care, being looked after by family members, are not included. This accounts for a large number of children who are removed from birth parents due to maltreatment. Children in kinship care may be included in future trials.

An additional limitation is that some children will change placement between baseline and follow up, meaning that there will be different respondents. If one intervention proves better at achieving permanent placements than the other, then the number of placement moves is likely to vary between the arms of the trial, thereby introducing bias. This creates a challenge in interpreting results, but the child's primary caregiver at the time is likely to be the best person to report on the child's health and development. 

Children are allocated randomly into GIFT or FACS, and while birth siblings will all be allocated to the same intervention, this will not be possible for nonsiblings placed in the same foster care home. If both birth families and foster families were allocated to the same intervention then this would lead to significant clustering effects; that is, potentially large groups of children (e.g., a large birth sibship spread across several foster homes and all the associated foster sibships) could require randomisation together creating imbalances. Consequently, some foster carers may have children in their care going through both the GIFT and FACS assessments which has the potential to introduce contamination.

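### Section 2.3 counts children but reports families, although families are randomised; the plan should give the number of families and say that the ITSEA comparison accounts for birth family

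*Protocol article*

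**What the plan says.** Section 2.3 builds the trial's size from a flow of children: "An estimated 153 eligible children are expected to enter care due to maltreatment during this period, that is, 9 children per month". The period is given as follows: "Recruitment is taking place over 17 months from December 2011 to April 2013". The consent rate is then applied and the unit changes: "An anticipated consent rate of 65% will include approximately 100 families in the study, with 50 children in each trial arm".

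The same section makes the family the unit of allocation: "The families are randomly allocated to GIFT or FACS by the Robertson Centre for Biostatistics". It adds: "Children from the same birth family, regardless of placement, are assigned the same study arm to reduce contamination". Section 2.2 admits children from 6 to 60 months, and the article states no rule of one child per family.

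On the efficacy analysis, section 2.9 says that "changes in scores on the ITSEA competence scale will be compared between the GIFT and FACS groups, adjusting for important baseline variables". It names no model and no family term. Clustering appears once, in section 3.1, as the reason for not also allocating foster homes together: "If both birth families and foster families were allocated to the same intervention then this would lead to significant clustering effects". That paragraph envisages a large birth sibship placed across several foster homes.

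**The concern.** Two things do not fit together.

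First, one sentence gives about 100 families and 50 children per arm. Both hold only if no two enrolled children are siblings. The sibling rule in section 2.3 and the sibships discussed in section 3.1 show that siblings are expected. The sentence that fixes the trial's size therefore overstates the number of randomised units.

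Second, allocating whole birth families creates clusters, and the published text does not carry this through to the comparison. Siblings share parents, an arm and the birth parents at whom the intervention is aimed, so their outcomes are likely to be correlated. Adjusting for baseline covariates does not in general remove that correlation.

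Two products of an exploratory trial are at stake: honest interval widths for the effect estimate, and design parameters for the next trial. Section 1 lists the required size of a definitive trial as a research question. Answering it for a family-randomised design takes the number of families, the mean number of eligible children per family and the family intraclass correlation (ICC).

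**Working it through.** **Step 1: reproduce the plan's figure.** Inputs from section 2.3: 9 children per month, 17 months, 65% consent.

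- 9 × 17 = 153 children
- 0.65 × 153 = 99.45 children, or about 50 per arm

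The figure reproduces as a count of children. No step converts children to families. The section states no alpha, power, effect size or standard deviation, so there is no power calculation to check.

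**Step 2: how many families could this be?** The documents give no sibship distribution, so three mixes are assumed. For each, with *p* the share of families with *m* eligible children, the mean sibship is Σ*pm*, and 100 children come from 100/Σ*pm* families.

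| Assumed share of families with 1 / 2 / 3 children | Mean sibship Σ*pm* | Families for 100 children | Size-weighted mean Σ*pm*²/Σ*pm* |
|---|---|---|---|
| 80 / 17 / 3% | 1.23 | 81 | 1.75/1.23 = 1.42 |
| 70 / 25 / 5% | 1.35 | 74 | 2.15/1.35 = 1.59 |
| 55 / 33 / 12% | 1.57 | 64 | 2.95/1.57 = 1.88 |

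If every family had one child, families and children would both number about 100 and nothing below would apply.

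**Step 3: consequence if children were analysed as independent.** Family sizes are unequal, so the design effect uses the size-weighted mean:

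- DE = 1 + (Σ*pm*²/Σ*pm* − 1) × ICC
- effective sample = 100/DE
- true level of a nominal 5% test = 2(1 − Φ(1.96/√DE))
- shortfall of a definitive trial sized without DE = 1 − 1/DE

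The ICC is also not given. It is ranged from 0.1 to 0.7. The low end is included because the residual correlation of a baseline-adjusted change score may be modest.

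| Mean sibship | ICC | DE | Correct SE ÷ unadjusted SE | Effective sample of 100 | True level of 5% test | Shortfall |
|---|---|---|---|---|---|---|
| 1.23 | 0.1 | 1.04 | 1.02 | 96 | 5.5% | 4% |
| 1.23 | 0.3 | 1.13 | 1.06 | 89 | 6.5% | 11% |
| 1.35 | 0.5 | 1.30 | 1.14 | 77 | 8.5% | 23% |
| 1.57 | 0.7 | 1.62 | 1.27 | 62 | 12.3% | 38% |

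The simpler equal-size formula, DE = 1 + (mean − 1) × ICC, gives smaller values. At mean 1.35 its multiplier of the ICC is 0.35, against 0.59 here. The size-weighted form is the appropriate one when children from unequal sibships are weighted equally.

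**The case against.** The strongest objection is that section 2.9 is a one-sentence summary in a condensed article. It specifies no model, variance estimator or independence assumption. A mixed model with a family random intercept, or family-robust standard errors, would fit that sentence, and the full analysis plan is not at hand. This stands. A reader might infer that the trial's standard errors will be too small. The documents do not establish that. They support only a conditional statement about what follows if children are treated as independent.

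It can also be said that the size is a recruitment projection for an exploratory trial. This stands too: no power is stated, so none is invalidated.

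The mislabel may look harmless, because the same sentence gives 50 children per arm and the Figure 1 caption refers to children. That limits the confusion about children. It does not supply the number of randomised units, which is the figure that is wrong.

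The magnitudes rest on assumed sibships and ICCs, and the 6 to 60 month window limits how many siblings can be eligible. That is correct, and at the low end the effect is small.

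Two further inferences should be resisted. Siblings might be thought to be rated mostly by one carer, which would raise the correlation. The article gives no frequency, and it envisages siblings in different foster homes. A design effect of 1.62 might also be read as a definitive trial 62% too small. It means that the required size is 62% larger, so the shortfall is 1 − 1/1.62, about 38%.

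**Conclusion.** The point holds in two parts of different strength.

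The count is wrong on the face of section 2.3. About 99 children are reported as about 100 families, and the number of randomised families will be below 100 if any siblings enrol: about 64 to 81 under the assumed mixes. This does not depend on anything in an unseen analysis plan.

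The analysis part is conditional. The comparison as described mentions only baseline covariates. If it treated children as independent, the design effect ignored would be about 1.04 to 1.62, and a nominal 5% test would run at about 5.5% to 12%. A definitive trial planned the same way would have about 4% to 38% fewer children than it needs. These ranges assume mean sibships of about 1.2 to 1.6 and a family ICC of 0.1 to 0.7, and they shrink to nothing if siblings are absent or uncorrelated. It would also be too strong to say that no design effect will reach the definitive trial: the text does not promise one, but nothing in it rules out estimating the ICC from the data.

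**What to change.** 1. In section 2.3, restate the size as approximately 100 children, about 50 per arm, from fewer than 100 birth families, and give the expected number of families.
2. In section 2.9, state that the ITSEA comparison accounts for birth family, through a random intercept for family or family-robust standard errors with a small-sample correction.
3. Name the birth-family ICC and the mean eligible sibship size as planned outputs, to be used in sizing the definitive trial.

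A crossed random effect for the baseline foster home could be added as a sensitivity analysis. It is optional and not part of the required change.

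The cost is wording and one model term, with no extra data beyond the family identifier that allocation already requires. Intervals will be slightly wider if siblings are correlated, and the stated number of families will be smaller.

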### 2.4. Care as Usual: Family Assessment and Contact Service (FACS)

FACS comprises a team of social workers, which undertakes an assessment of the child and the family in order to make a decision about the child's future care. It examines family functioning and makes recommendations regarding placement outcomes for children. It is able to refer family members onto additional services (e.g., drug rehabilitation). Although FACS is an established service in Glasgow, it was previously a specialised team assessing only small numbers of children. As the delivery of early assessment services in Scotland was known to be highly heterogeneous, FACS will offer a new level of consistency and therefore is considered to be “enhanced services as usual”. Any child whose parent or foster carer does not consent to participate in the research study will therefore receive the service from FACS.

### 2.5. The Trial Intervention: Glasgow Infant and Family Team (GIFT)

GIFT is a structured intervention with the primary goal of rehabilitating the child back with their primary caregiver, when it is safe to do so. The team is multidisciplinary incorporating social workers, psychologists, a psychotherapist, and a psychiatrist. Like FACS, GIFT makes an assessment of the children in the context of their relationships with their caregivers. Whilst both teams assess relationships with the birth parents, GIFT also always assesses the relationships with foster carers. GIFT arranges referrals onto other services as described in FACS. GIFT also offers an intensive relationship focussed intervention to every birth family, which is anticipated to take between 6 and 9 months. This intervention is aimed at improving the relationship between the child and his/her birth family and according to the outcome, GIFT recommends whether the children should return home or be adopted. The intention is that all foster carers who care for children coming to the GIFT intervention should be jointly registered as potential adopters so that, if rehabilitation home is not feasible, the child does not have to experience another change of placement before achieving permanency. However, it is likely that this will take time to achieve and that not all carers will be dually registered within the recruitment period.

### 2.6. Outcome Measures

Baseline assessment based on the outcome measures is administered at a minimum of one month after the child is received into care. One month is allowed to let the carer get to know the child as well as to allow for the child to settle into the carer's home. Follow up assessment of the outcome measures is then repeated one year later. At baseline, the assessment is completed for all children with their foster carers. At follow up, the assessment is completed with the child's primary caregiver at that time who may be the birth parent, adoptive parent, or the foster carer—who may be the same or different from the foster carer at baseline. 

### 2.7. Primary Outcome Measure

Infant mental health is measured using the Infant-Toddler Social and Emotional Assessment (ITSEA) [12, 13]. This 166-item questionnaire is well validated and is completed by the parent or carer [14]. It covers a wide range of social and emotional behaviours in infants, across four domains: externalising, internalising, dysregulation, and competence. It has been used successfully in previous interventions research with maltreated children showing medium to large effect sizes and good longitudinal stability [15]. 

### 2.8. Secondary Outcome Measures

A cognitive assessment of the child is undertaken. Children under 2.5 years are assessed with the Bayley Scales of Infant Development [16], while children 2.5 years and over are assessed using the Wechsler Preschool and Primary Scale of Intelligence (WPPSI IV) [17]. The parent or carer also completes the Parent Evaluation of Development Status (PEDS) [18] which assesses cognitive milestones including language, the Disturbances of Attachment Interview (DAI) [19] which identifies symptoms of attachment disorders, the Parent-Infant Relationship Global Assessment of Functioning (PIR-GAS) [20] which assesses global relationship functioning following observation of both play and meal time activities, and the Paediatric Quality of Life Inventory (PedsQL) [21] which assesses health-related quality of life. The Development and Well-being Assessment (DAWBA) [22] is completed by carers with a child aged two and above and is used to generate International Classification of Diseases (ICD) and Diagnostic and Statistical Manual of Mental Disorders (DSM) codes. The Waiting Room Observation (WRO) [23], a structured observation for symptoms of attachment disorders, is also completed by the researcher when the child and carer first arrive at the clinic. In addition, the Strange Situation Procedure (SSP) [24], the gold standard measure of infant/toddler attachment patterns, is completed at the follow-up time only. 

In addition, the “This Is My Baby” (TIMB) [25] interview, which assesses the degree of commitment to the child by the foster carer is included as it may be investigated as a potential moderator between maltreatment and outcome.

In this exploratory trial, the feasibility, reliability, and developmental appropriateness of each measure will be examined in order to select the best measures for a definitive trial. In addition, the potential for linkage of data with routinely collected data on health and social care and, in the future, education and legal services will be explored. 

